#### Mesopic microperimetry

Mesopic microperimetry using the MAIA (Macular Integrity Assessment; Centervue SpA, Padova, Italy) assesses central visual function, whilst using fundus-tracking technology to improve test accuracy and reliability [18]. This is a highly useful test as it produces a central threshold sensitivity map with clear and easy to interpret results indicating visual function capabilities. We have shown that microperimetry is a useful, repeatable clinical marker in other inherited retinal diseases [19, 20]. Microperimetry was a main outcome measure in the phase I/II gene therapy clinical trials for *RPGR*-associated RP [21]. Application and utility assessment are still required in other RP subtypes due to the disease’s heterogeneity. Mesopic microperimetry will be used as a marker to identify disease severity and to compare with the other visual function results.

Microperimetry will be performed on all participants completing part one, in a darkened room (light level < 1.0lx), without any formal dark adaptation or any pharmacological pupil dilation [22, 23]. The standard 10−2 test grid (Fig. 3A) will be used, with 4−2 bracketing threshold strategy. Examination involves the presentation of Goldmann size III stimuli of various intensities (0-318cd/m^2^), presented for 200ms, on to a mesopic background (1.27cd/m^2^). The overall dynamic testing range is 0-36dB. A 1-degree diameter red circle will be used as a central fixation target. Prior to testing, subjects will be told about the test and what they are required to do. The right eye is to be tested first followed by the left eye as per clinical convention. The non-tested eye must be occluded throughout.

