### Part two

#### Scotopic Microperimetry

Scotopic microperimetry is a modified version of microperimetry, that is performed at much lower light levels, using two-colour perimetry to target a spatial assessment of rod and cone photoreceptor scotopic function [24]. For clinical trials, this test could be incredibly useful in identifying rod or cone specific photoreceptors responding to treatments. However, this test can be more difficult for patients to complete, it is prone to ceiling and floor effects [18]. Clinical utility assessment of scotopic microperimetry in patients with RP at different disease stages is vital to enable us to understand whether it is likely to be a practical and appropriate measure.

Scotopic microperimetry testing, will be performed on the S-MAIA microperimeter. Each participant must complete 20 minutes of dark adaptation (light level < 1.0lx) prior to testing [25]. The 37-point scotopic wide radial grid will be used (Fig. 3B), with a 4−2 bracketing threshold staircase strategy and Goldmann size III (0.43degrees) stimulus. Cyan stimuli testing (505nm) is performed first followed by red stimuli (627nm) testing. A 1-degree circular red fixation target (645nm) is used, if this is not seen at the minimum brightness, the luminance will be increased until the fixation target is detected. No formal break will be given between each test. A subset of patient and healthy control participants (at least 50%) will undergo repeat testing on one eye only for repeatability analyses.

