### Statistical analysis

#### Study sample size

There is insufficient data on the variance of most of these visual function tests, since many have not been used in patients with inherited retinal disease and more specifically, rod-cone degeneration, to enable accurate method comparison and power calculations. The data obtained from this study will be used to estimate power and calculate sample sizes in future clinical trials. Therefore, we apply a pragmatic sample size estimation. On average 30 patients a week attend the eye hospital with inherited retinal disease.

Around 40% of patients with inherited retinal disease have RP [27]. From this we calculate 12 patients with RP attend the eye hospital per week on average. Not all will be eligible. Those with advanced disease resulting in unmeasurable vision will be excluded. We estimate 50% will be eligible. Patients are referred to our tertiary referral centre to learn more about their condition and enquire about research. From previous studies, patient recruitment rate has been good, with at least four in five patients willing to take part in research studies. We estimate there will be four eligible patient participants willing to take part each week. The project must work around other research and clinic availability.

We have allocated 15 months (65 weeks) for data collection. To avoid patient and participant inconvenience and clinic disruption, it will not be possible to test more than two participants in one day. Some weeks we will be able to complete testing for two participants (particularly if they are together), while other weeks it may be only possible to complete one. Therefore, we have set a conservative target of 1–2 participants per week. From this we generated an estimated sample size of 40 patient participants and 40 healthy volunteer participants. We believe 80 participants is achievable and will provide sufficient end-to-end data distribution for this early-stage study. Our work investigating tests in other eye disease have used similar sample sizes [19, 28].

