#### Assessment of clinical utility & statistical methods

Smart’s clinical utility multi-dimensional model will be used to comprehensively explore the clinical effectiveness but also evaluate the tests ease and efficiency of use, their relevance and more importantly patient’s and participant’s perspectives [30]. The model is broken down into four aspects but there is some overlap between these:

Appropriateness – are the tests effective and relevant?Accessibility – are they readily available and affordable?Practically – are they functional and straightforward?Acceptability – are they ethical and of acceptable patient burden?

To assess appropriateness and practicality of these new assessments we will apply descriptive statistics to indicate the number of participants able to complete each test. Followed by distribution plots and frequencies to indicate the spread of data. An appropriate visual function test is one that shows a large range of results across the disease spectrum with limited ceiling and floor effects. It should distinguish between healthy controls and patient participant’s vision. To investigate this, comparative statistics will be applied. The degree of difference will be analysed using Cohen’s D to calculate the effect size. ANOVA or non-parametric equivalents will be used to test for statistically significant differences, between patients and controls. The threshold of statistical significance will be set at p < 0.05. Test time will be measured and used as a quantitative marker for accessibility.

To investigate test-retest variability, a subset of participants will complete the study tests to enable Bland-Altman repeatability analyses with resulting limits of agreement and coefficient of repeatability indices. This will identify a clinically significant criterion [31]. Patient participants may be categorised by their genotype and their clinical characteristics, to develop greater understanding of genotype-phenotype correlations.

Regression analyses will be applied to compare the new visual function test results to currently used measures including VA, patient reported outcome measure questionnaires and ocular imaging structural analyses. A strong correlation would suggest tests are assessing similar aspects of the patient’s vision. This is important since it can help us understand which visual function assessments may be more relevant to specific patient reported experiences. Missing or incomplete data will be excluded from analyses.

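### For scotopic microperimetry, pairs with both readings at the floor or ceiling will narrow the Bland-Altman limits, so the change criterion taken from them is too small where vision is measurable

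*Protocol article*

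**What the plan says.** In the Protocol article, the section on assessment of clinical utility and statistical methods names the repeatability method as "Bland-Altman repeatability analyses with resulting limits of agreement and coefficient of repeatability indices". It gives the result a use in the next sentence: "This will identify a clinically significant criterion". The one rule on which data enter closes the section: "Missing or incomplete data will be excluded from analyses".

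The Scotopic Microperimetry section says of that test that "it is prone to ceiling and floor effects". It fixes the grid ("The 37-point scotopic wide radial grid will be used") and the repeat sample: "A subset of patient and healthy control participants (at least 50%) will undergo repeat testing on one eye only for repeatability analyses". For the mesopic test the scale is explicitly bounded: "The overall dynamic testing range is 0-36dB". No range is given for the scotopic test.

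The sample size section gives the results a further use: "The data obtained from this study will be used to estimate power and calculate sample sizes in future clinical trials".

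The statistical methods section also makes limited floor and ceiling effects a mark of an appropriate test, to be looked at with distribution plots and frequencies. Nothing links that check to the repeatability analysis.

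**The concern.** A repeatability coefficient is meant to say how far two readings can differ when nothing has changed. A location below the instrument's floor on both occasions records the same value twice, so its difference is exactly zero. That zero reflects the scale and carries no information about measurement error, yet it enters the SD of the differences as perfect agreement. Ceiling pairs, for example in healthy controls, do the same.

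A recorded bound value is neither missing nor incomplete, so the stated exclusion rule leaves these pairs in. The article fixes the estimator, the exclusion rule and the use of the result, and it expects the kind of data on which that combination fails.

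At stake is the threshold that separates real change from noise. If it is too small, ordinary noise at measurable locations or eyes is read as change. A variance taken from the same pairs would also be too optimistic for planning later trials in patients with measurable function.

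**Working it through.** **The plan's own figure.** There is none to reproduce. The article gives no within-test SD, coefficient, limits or share of readings at a bound. The number of repeat pairs follows from the text: at least 50% of 40 is 20 patients and 20 controls, if all 80 complete part two (assumption).

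**Step 1: direction.** Setting values outside the range to the bound can never enlarge the difference within a pair. With no systematic shift between test and retest, the SD of differences can only fall.

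**Step 2: simple mixture.** Let a share f of pairs sit at a bound twice (difference 0) and let the rest have differences with SD s. The SD over all pairs is s × √(1 − f), and the coefficient 1.96 × SD shrinks by the same factor. For an unchanged measurable pair with normal differences, the chance of exceeding the shrunken criterion is 2 × [1 − Φ(1.96 × √(1 − f))].

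| f | √(1 − f) | Shortfall | False-change rate (nominal 5%) |
|---|---|---|---|
| 10% | 0.949 | 5% | 6.3% |
| 30% | 0.837 | 16% | 10.1% |
| 50% | 0.707 | 29% | 16.6% |

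**Step 3: clipped readings, by location.** Assumptions: true values normal with SD 8 dB, within-test SD 2 dB, readings clipped to 0-36 dB (the mesopic range, borrowed because no scotopic range is given), and the mean varied to change the floor share. The unclipped coefficient is 1.96 × √2 × 2 = 5.54 dB. The false-change rate is for true values between 6 and 30 dB.

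| Pairs at a bound twice | All pairs, dB | Shortfall against 5.54 | False-change rate | Neither reading at a bound, dB |
|---|---|---|---|---|
| 9% | 5.17 | 7% | 6.8% | 5.44 |
| 23% | 4.63 | 16% | 10.2% | 5.33 |
| 44% | 3.79 | 32% | 18.2% | 5.21 |
| 54% | 3.36 | 39% | 23.7% | 5.13 |
| 68% | 2.72 | 51% | 33.6% | 5.05 |

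The shortfall exceeds the mixture figure because pairs with one reading at a bound are also compressed. Using only pairs with neither reading at a bound leaves a shortfall of 2% (5.44/5.54) to 9% (5.05/5.54).

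**Step 4: eye mean over 37 points.** Assumptions: point error SD 3 dB plus an error of SD 1 dB shared by all points of a session. The unclipped coefficient is 1.96 × √[2 × (1 + 9/37)] = 3.09 dB. Simulated values with clipping are 2.74, 2.36, 1.81 and 1.22 dB at 9%, 22%, 42% and 65% of points floored twice. Averaging over the grid therefore does not remove the effect.

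**Step 5: comparison of two tests in the same unit.** With equal within-test SD of 2 dB, a test with 54% floor pairs shows 3.37 dB and one with about 1% at a bound shows 5.44 dB. If the floored test is truly noisier, it still looks better at SD 3.2 dB (5.29) but no longer at 3.6 dB (5.91). By the mixture formula, a true SD ratio above 1/√(1 − f) restores the right order: 1.20 at f = 30% and 1.41 at f = 50%.

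**The case against.** The strongest reply is that the article never says all readings are used. It has one sentence on the method, does not say whether the unit is a location or an eye, and condenses a fuller protocol. Handling of bound values is ordinary analysis-plan content. This stands in part: the inclusion of bound pairs is inferred, and a fuller plan may already restrict it. But the estimator, the sole exclusion rule and the use of the result are all stated, and followed as written they give a biased criterion.

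Second, the size rests on assumptions, since the floor share, the error SD and the unit are not given. At 10% bound pairs the 5% shortfall is small beside sampling error: with 20 pairs the 95% interval for the coefficient runs from about 0.76 to 1.46 times the estimate. That is fair, though unlike sampling error the bias has one direction and does not shrink with more pairs.

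Third, floor and ceiling effects are judged separately under appropriateness, and a Bland-Altman plot would show clustering at the bound. This partly protects the choice of test. It does not correct the criterion.

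Fourth, unmeasurable vision is excluded and the target is early-to-moderate disease. The logMAR 1.0 entry limit makes floor pairs unlikely for standard acuity. That limit does not bound scotopic sensitivity, so the point narrows to scotopic microperimetry and any other test found to have many readings at a bound.

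A reader might go further and infer that the test with the worst floor will look the most repeatable, and that this distorts a primary ranking of tests. The document does not support that. It plans no ranking by coefficient, and it does not place scotopic microperimetry under the primary outcome, which concerns current tests. The reversal also needs a common unit (cyan against red in dB, not logMAR against dB) and similar true error.

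**Conclusion.** The concern holds in a limited form. For scotopic microperimetry, limits and coefficients that include pairs at a bound on both readings will be too narrow, and the change criterion will be too small for measurable locations or eyes. The mixture figures (5%, 16% and 29% at 10%, 30% and 50% of such pairs) rest on an assumed share and on no systematic test-retest shift. Under the assumed models the clipped simulations give somewhat larger shortfalls. If the share turns out to be only a few percent, the effect is negligible.

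A heavily floored test can look more repeatable than another in the same unit with similar true error, but that is a conditional side effect. This should be changed before analysis; it does not undermine the study's design.

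**What to change.** In the statistical methods section, state how readings at a bound enter the repeatability analysis:

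- Report, for each test and separately for patients and controls, the share of test-retest pairs with one or both readings at the floor or ceiling, beside each coefficient.
- Derive the change criterion from a model that treats bound readings as censored (for example a censored mixed model), or from pairs with neither reading at a bound. For the second option, note the small remaining downward bias (2% to 9% in the simulation above).
- Show the limits by level of mean sensitivity, so that the criterion is not one pooled figure across floored and measurable retina.
- Say whether the unit is the location or the eye mean, since the size of the effect depends on it.
- Use the same estimates for any later power calculation in patients with measurable function.

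No new data are needed. The cost is a little more analysis work, fewer usable pairs if bound readings are dropped, and a wider criterion that makes the test look less sensitive to change.

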**Methods:**

This cross-sectional study involves two participant groups, patients with inherited retinal disease (n = 40) and healthy controls (n = 40). The study has been designed to be flexible and run alongside NHS clinics. The study is split into two parts. Part one includes examining standard visual acuity, low luminance visual acuity, the Moorfields acuity chart visual acuity, mesopic microperimetry and three separate patient reported outcome measures. Part two involves 20 min of dark adaptation followed by two-colour scotopic microperimetry. Repeat testing will be undertaken where possible to enable repeatability analyses. A subset of patients with inherited retinal disease will be invited to participate in a semi-structured interview to gain awareness of participants’ thoughts and feelings around the study and different study tests.

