### Study procedures

Informed consent will be obtained, in person, by the investigator (appointed research optometrist) prior to completing any study procedures. This is a single visit study that has been carefully designed to fit in and around the NHS outpatient appointments at Oxford Eye Hospital, to minimise the need for participants to return to the eye hospital to take part in the study on a separate day. This is important as the specialist retinal genetic clinics are part of a tertiary referral centre, meaning that patients travel from all over the country to attend. The study has been planned to be as flexible as possible to work around time and room availability constraints, therefore not all the study tests are required to be completed. The study is divided into two parts, part one and part two (Fig. 1). Participants must complete all tests in a single part, although where possible participants will be invited to complete the entire study. A subset of patient participants will be invited to take part in semi-structured qualitative virtual interviews upon completion of the study. Estimated study duration is one hour for each part, two hours in total for the entire study.

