**Fig. 2 Fig2:**
[figure not shown]
(**A**) is an example of the standard ETDRS chart. (**B**) illustrates low luminance visual acuity, simulating the view of the ETDRS chart through the 2.0 log unit neutral density filter. (**C**) is the Moorfields Acuity Chart

Low luminance VA (Fig. 2B) will be measured first following refraction, using a 2.0 log unit neutral density filter placed in front of the patient’s right eye, with the room lights switched off and using the retro illuminated standard ETDRS visual acuity chart (luminance 1.6 cd/m^2^). The none testing eye will be occluded throughout. Table 2 details the VA test, eye and corresponding letter chart (R, 1 or 2) testing order. The letter charts are rotated at each assessment to limit any letter sequence memorisation.

**Table 2 Tab2:** Visual acuity, eye and corresponding letter chart testing sequence

Visual acuity testing sequence and letter chart rotation
1. Refraction of both eyes, using chart R
2. Right eye low luminance VA, left eye occluded, chart 1
3. Right eye standard VA, left eye occluded, chart 1
4. Left eye low luminance VA, right eye occluded, chart 2
5. Left eye standard VA, right eye occluded, chart 2
6. Repeat right eye low luminance VA, left eye occluded, chart R
7. Repeat right eye standard VA, left eye occluded, chart R
8. Binocular low luminance VA, chart 1
9. Binocular standard VA, chart 1
10. Left eye MAC VA, right eye occluded chart 2
11. Right eye MAC VA, left eye occluded, chart 1
12. Repeat left eye MAC VA, right eye occluded, chart 2
13. Binocular MAC VA, chart 1

The Moorfields Acuity Chart (MAC) is a modified version of the ETDRS letter chart (Fig. 2C), it has been developed to be a more sensitive measure of early changes in central cone photoreceptor disease in age-related macular degeneration. The chart uses vanishing optotypes, whereby, once the letter is no longer recognisable it is also undetectable [8]. MAC chart assessment follows LLVA and standard VA assessment, with the room lights switched on. Again, table 2 details the eye testing order and corresponding chart to use.

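### The repeatability coefficient is presented as a criterion of clinical significance, but it measures only same-visit test-retest noise and is expected to be a lower bound for detectable change between visits

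*Protocol article*

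**What the plan says.** Under *Assessment of clinical utility & statistical methods*, the Protocol article says that a subset of participants will be retested to allow "Bland-Altman repeatability analyses with resulting limits of agreement and coefficient of repeatability indices". The next sentence gives the interpretation: "This will identify a clinically significant criterion". It carries a literature citation but no definition of clinical significance.

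The timing of the retests follows from the design. *Study procedures* states: "This is a single visit study that has been carefully designed to fit in and around the NHS outpatient appointments". It estimates one hour for each part and two hours in total. Table 2 places the acuity repeats in the same sequence as the first measurements, for example "6. Repeat right eye low luminance VA, left eye occluded, chart R" and "12. Repeat left eye MAC VA, right eye occluded, chart 2". For scotopic microperimetry the article says: "A subset of patient and healthy control participants (at least 50%) will undergo repeat testing on one eye only". No retest on another day is described.

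Reliability is named in both the primary and the secondary outcome. *Study sample size* says that the data will be used for power and sample size calculations in later trials.

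**The concern.** The sentence makes two steps that the analysis cannot support.

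1. **From noise to clinical importance.** A coefficient of repeatability says how far two readings on an unchanged person may differ. It answers whether a difference exceeds measurement error. Whether that difference matters to the patient needs outside evidence, such as an anchor to a patient-reported measure, and none is tied to this step.
2. **From one session to two visits.** A trial change score compares readings from different days. It also contains day-to-day variation in the patient, the set-up, the refraction and the state of adaptation. Two readings in one visit share most of that, so their difference leaves it out.

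Reliability estimates are a main product of this study. A same-visit limit published under a label of clinical significance could be taken up in later trial planning as though it covered change between visits and carried patient meaning.

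**Working it through.** **No figure to reproduce.** The article states no coefficient, no within-person standard deviation and no change threshold for these tests, and it says that variance data are insufficient for most of them. Its only external benchmark for change, the 15-letter gain in the *Background*, concerns standard visual acuity and is not linked to repeatability. The direction can be derived; the size needs an assumption.

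**Timing, from Table 2**

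| Test | First | Repeat | Charts |
|---|---|---|---|
| Low luminance VA, right eye | step 2 | step 6 | 1, then R |
| Standard VA, right eye | step 3 | step 7 | 1, then R |
| Moorfields chart, left eye | step 10 | step 12 | 2, then 2 |

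All are within one sitting. The Moorfields repeat uses the same chart number for the same eye, although the text above the table says that charts are rotated at each assessment to limit memorisation. Letter recall could make that pair agree more closely than it should.

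**Effect of leaving out between-visit variance.** Let Sw² be the within-session variance, Sb² the visit-to-visit variance in a stable person, and r = Sb²/Sw².

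- Same-visit coefficient: 1.96 × √2 × Sw = 2.77 Sw.
- Limit for two visits: 1.96 × √2 × √(Sw² + Sb²) = 2.77 Sw √(1 + r).
- Ratio of the two: √(1 + r), which is above 1 for every r above 0.
- Share of stable patients beyond the same-visit limit when seen at two visits: 2 × [1 − Φ(1.96/√(1 + r))], in either direction.

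The values of r are assumed:

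| r | √(1 + r) | Same-visit limit too small by | 1.96/√(1 + r) | Stable patients flagged |
|---|---|---|---|---|
| 0 | 1.00 | 0% | 1.960 | 5.0% |
| 0.10 | 1.05 | 4.7% | 1.869 | 6.2% |
| 0.25 | 1.12 | 10.6% | 1.753 | 8.0% |
| 0.50 | 1.22 | 18.4% | 1.600 | 11.0% |
| 1.00 | 1.41 | 29.3% | 1.386 | 16.6% |

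By symmetry, half of each flagged share would look like improvement.

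**Sampling error of the coefficient.** This is a separate matter. The 95% limits, as multiples of the estimate, are √(df/χ²₀.₉₇₅) and √(df/χ²₀.₀₂₅).

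- Scotopic microperimetry: the 50% minimum of 40 patients is 20 pairs, if all 40 complete part two. With 19 df: √(19/32.85) = 0.76 and √(19/8.91) = 1.46.
- Acuity tests: 40 pairs if every patient completes part one, because the repeats are listed steps. With 39 df: √(39/58.12) = 0.82 and √(39/23.65) = 1.28.

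**The case against.** **The phrase may mean only change beyond noise.** The sentence rests on a cited source that is not at hand, and that source may use the term in this sense. The article also looks for relevance elsewhere, by regressing test results on patient-reported measures and by interviewing patients. This has weight, but those analyses are not used to set the criterion, and a reader will take clinically significant at face value. If only noise is meant, the rewording loses nothing.

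**The shortfall may be partly offset.** The *Safety* section accepts that testing can be tiring, and scotopic testing has no formal break between tests. Fatigue or learning that differs between people would widen a same-visit coefficient. This stands, and for that reason the coefficient is only *expected* to be a lower bound.

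**Stronger readings that a reader might infer, and that the article does not support:**

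- *The study's stated purpose is to set change thresholds for regulators, with the coefficient as a responder cut-off.* The article speaks of identifying suitable outcome measures and informing sample sizes. Its *Discussion* reports a view that mean change is a better acuity endpoint than a binary cut-off. No section says that the coefficient will classify trial patients.
- *The retested subset favours fitter participants.* The abstract does say "Repeat testing will be undertaken where possible to enable repeatability analyses", but Table 2 makes the acuity repeats fixed steps, and *Study procedures* requires all tests in a part to be completed and attributes the flexibility to time and rooms. Selection by stamina is speculation.
- *Floor effects shrink the coefficient by a known amount across the tests.* Among the tests under study, the article calls only scotopic microperimetry prone to floor and ceiling effects, and it gives no share of readings at either end. The direction is plausible there; no size can be given.

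**Conclusion.** The point holds as a fault in a stated rule of interpretation, and it should be corrected.

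That repeatability is not clinical significance needs no assumption. That a same-visit coefficient is too small for change between visits needs only Sb² above zero, less any widening from uneven fatigue or learning. The size does rest on assumption: 6% to 17% of stable patients flagged, instead of 5%, for r from 0.10 to 1.00, with normal differences and visit effects that are independent between visits. The article does not fix where in that range, or outside it, any test lies. Nor does it say that patients and controls will be pooled, so reporting them separately is a safeguard and not the correction of an error.

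Data collection is unaffected. The harm lies in the label that later trials would inherit.

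**What to change.** Replace the sentence on the criterion with: *This gives the within-session repeatability limit, the smallest difference distinguishable from same-visit measurement noise; it is expected to be a lower bound for detectable change between visits and is not a threshold of clinical significance.*

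In the analysis:

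- Report the coefficient for patients separately from controls, with its 95% confidence interval.
- Carry the upper confidence bound into future trial planning: about 1.46 times the estimate with 20 scotopic patient pairs, or 1.28 times with 40 acuity pairs. This bound covers sampling error only and does not supply the missing between-visit variance.
- For scotopic microperimetry, report the share of pairs at floor or ceiling on both runs, and give the coefficient with and without them as a sensitivity analysis.

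The cost is one sentence and a few lines of analysis, with no added test or visit. The downside is a weaker claim and a larger quoted limit.
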